**Figure 1 F1:**
[figure not shown]
**Flowchart of the PREPASE study.** BM = baseline measurement. M = Measurement. The first session starts 1 month after the BM and take place once per month during 6 months. The measurements take place every 3 months after the BM.

Blinding of participants or members of the research team for this study is not possible. However, prior to randomization the participants receive limited information on the intervention program. Participants are informed that the study aims at testing a program to help parents prevent PS exposure in their children and to study the relationship between PS exposure and respiratory complaints in children.

After randomization, parents receive more information about their group allocation. All visits are planned for the entire study period, and a confirmation letter is sent to the participants including information and materials with instructions for the urine sampling and lung function measurements in children.

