### Randomisation

Eligible families are contacted by phone to ensure eligibility and willingness to participate in the study. Eligible families, after giving written informed consent, are randomized into one of the two groups, the intervention group or control group, with an allocation ratio of 1 (see Figure 1). A database logistic system is made for the study by MEMIC (Centre for data and information management, MUMC+), and includes a randomization system. Families are pre-stratified according to the age of the child, <6 years and ≥6 years, to prevent chance imbalances between the intervention and the control group with respect to age and age-related variables, such as lung function and possible parental attitude towards passive smoking (parents with younger children may evaluate PS exposure differently from parents with older children). Separate randomization lists are generated for each stratum to ensure treatment group assignments are balanced within each stratum.

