### Outcomes

An overview of the measurements is provided in Table 2. All measurements are home-based and all questionnaires are completed by the parents.

**Table 2 T2:** Overview of the outcome measurements

	***Time (months)***	**0**	**3**	**6**	**9**	**12**

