### Primary outcome measures

#### Eliminating or reducing PS exposure in children

PS exposure is measured with a standard questionnaire (at baseline and at 3, 6, 9, and 12 months after the baseline measurement) and is checked by urine cotinine concentrations of the children. In the PREPASE study, the percentage of parents eliminating or reducing PS exposure in children at home at 6 months (directly after the intervention program) is compared between the intervention and the control group. Eliminating or reducing PS exposure in children can be achieved ideally by parents stopping active smoking or less ideally by parents smoking outside the house.

PS exposure in children is measured with the following questions: “Do you smoke in the presence of your child?” (yes/no) If yes, “Where do you smoke in the presence of your child and does this occur always, regularly, sometimes or never?” (Parents are asked to provide an answer for the following locations: living room, own bedroom, child’s bedroom, kitchen, under the hood, hall, dining table/room, attic, rest/bathroom, balcony, garden, car, other) “On average, how many tobacco products do you smoke per day in the house while your child is present at the moment?” (xx cigarettes/cigars/pipe per day) “On average, how many tobacco products do you smoke per day outdoors while your child is present at the moment?” (xx cigarettes/cigars/pipe per day). Furthermore, parental report is verified by the child’s urine cotinine concentration.

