#### Urine cotinine of the children

Cotinine is the major metabolite of nicotine and can be detected in several bodily fluids, such as blood serum, saliva and urine [33]. Urine samples are collected (at baseline and after 3, 6, 9, and 12 months after the baseline measurement) and analysed for cotinine using the gas chromatography–mass spectrometry technique, Thermo Scientific DSQIII (Axel Semrau GmbH & Co. KG, Sprockhövel, Germany). Samples from children who have not yet been trained to go to the toilet are collected by placing a highly absorbent cotton wool in the diapers. Samples from toilet trained children are collected with a standard urine collection cup. Early-morning urine samples are collected on the day of the measurements by the RA or primary researcher. The urine samples are analysed at Medical Laboratory Humicon, B.V., Maastricht, the Netherlands. The laboratory receives the urine samples on the same day and stores them at 2-8° Celsius and analyses them within 1–2 weeks. The samples are provided with a numerical ID, the child’s birth year, date and time of collection. The laboratory is blinded to subjects’ identity and group assignment.

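### The statement that the research team cannot be blinded is too broad: it leaves the primary-outcome classification, which can be masked, open to arm-aware judgement

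*Protocol article*

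**What the plan says.** **Blinding.** The Randomisation section of the Protocol article says that "Blinding of participants or members of the research team for this study is not possible". The text around it concerns what families are told before and after allocation. One masked step appears elsewhere, under Urine cotinine of the children: "The laboratory is blinded to subjects’ identity and group assignment".

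**Primary outcome.** Under Primary outcome measures, "the percentage of parents eliminating or reducing PS exposure in children at home at 6 months (directly after the intervention program) is compared" between the arms. Success "can be achieved ideally by parents stopping active smoking or less ideally by parents smoking outside the house". The exposure report comes from parents: "All measurements are home-based and all questionnaires are completed by the parents". It covers smoking in the child's presence, a list of locations graded by frequency, and daily indoor and outdoor counts. Both parents complete the smoking questionnaire where applicable (Parental smoking behaviour). Then: "Furthermore, parental report is verified by the child’s urine cotinine concentration". The primary research question and the Statistical methods repeat that the report is checked or verified with cotinine.

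**Who sees what.** Two research assistants deliver the counselling, and cotinine feedback is part of sessions 2, 4 and 6. Urine is collected by a research assistant or the primary researcher. Control families receive their results only after the study (Control group).

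**Data system.** "A database logistic system is made for the study by MEMIC", which the article describes as a centre of the university hospital where the trial runs; the system includes the randomisation.

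**The concern.** The primary outcome is a derived verdict. Graded locations, indoor and outdoor counts, sometimes two parents' answers and a continuous cotinine value must become one yes or no. Some families will be discordant: the parent reports less smoking, but the child's cotinine is unchanged or higher. Somebody has to decide what those families count as, and how large a fall supports a report.

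Parents know their arm, so cotinine is the objective check on the primary outcome. If the criterion for that check, or the verdict on discordant families, is settled with the arm in view, the check is weakened, most plausibly in favour of the intervention. Laboratory blinding protects the measured value but not the verdict built on it.

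Families and counsellors cannot be masked. Classifying coded answers and coded cotinine values needs no contact with the family, so it can be.

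**Working it through.** **1. Which steps are masked, and which could be**

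| Step | What the article says | Could it be masked? |
|---|---|---|
| Counselling | Not masked | No |
| Parental report | Parents know their arm | No |
| Urine collection | Research assistant or primary researcher | Not at issue here |
| Cotinine assay | Laboratory masked to identity and group | Already masked |
| Deriving eliminated or reduced, verified | No classifier named; general statement that the team cannot be blinded | Yes, from coded data |

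**2. Is there a rule that would leave no room for judgement?** The primary research question, the primary outcome section and the Statistical methods all use eliminating or reducing, with a cotinine check. None gives a size of reduction, a cotinine level or fall, or a rule for discordance.

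**3. Could arm-linked results inform such a judgement?** Yes. Counsellors handle intervention-arm cotinine during the trial (sessions 2, 4 and 6). The article does not say which sample is fed back at each session, or whether staff see control-arm values as they accrue.

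**4. The plan's own sample size, for scale.** Inputs from Sample size calculation: 10% versus 30%, two-sided alpha 0.05, power 80%. Pooled-variance formula, mean rate 0.20:

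n per arm = [1.96 × √(2 × 0.20 × 0.80) + 0.8416 × √(0.10 × 0.90 + 0.30 × 0.70)]² / 0.20² = (1.109 + 0.461)² / 0.04 ≈ 61.6, so 62 per arm and 124 in total.

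The plan states 126, which is consistent; 63 per arm gives 80.9% power. For drop-out, 126 / 0.85 = 148.2, against 148 stated. Masking the classification changes none of this.

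**5. Illustration of size (assumed inputs, none from the document).** Spurious difference = discordant share × difference in acceptance between arms.

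- 20% discordant, acceptance differing by 25 points: 0.20 × 0.25 = 0.05, or 5 points.
- 20% discordant, acceptance differing by 50 points: 0.20 × 0.50 = 0.10, or 10 points.

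**6. What an error of that order does to the test (also assumed).** Suppose there is no true effect, 63 families per arm, and a share f of intervention-arm non-successes is wrongly credited. The observed intervention rate is p + (1 − p)f, where p is the true rate in both arms.

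| True rate p | f | Observed intervention rate | Two-sided rejection rate |
|---|---|---|---|
| 10% | 0 | 10% | 5.0% |
| 10% | 5% | 0.10 + 0.90 × 0.05 = 14.5% | 12.0% |
| 10% | 10% | 0.10 + 0.90 × 0.10 = 19.0% | about 30% |
| 20% | 5% | 0.20 + 0.80 × 0.05 = 24.0% | 8.4% |
| 20% | 10% | 0.20 + 0.80 × 0.10 = 28.0% | 18.2% |

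Steps 5 and 6 show sensitivity. They do not estimate bias in this trial.

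**The case against.** **No arm-aware classifier is named.** A reader might infer that the protocol hands the verdict to staff who know the arm. It does not say so: it names nobody and does not say that classification is case by case. The blinding sentence sits among remarks on what participants are told. This stands, and the point is limited to the step being left open.

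**Masked derivation is commonly left to the analysis plan.** Silence on it in a journal article would be no finding, and the analysis plan may well fix the rule. But the sentence on blinding is a positive statement. As worded it excludes any masked step for the research team, and a cut-off set elsewhere would not correct it.

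**A locked algorithm makes masking redundant.** This is largely true once the rule exists and decides every case. The rule must still be chosen, and any case it cannot decide resolved, before group-labelled outcomes are seen.

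**The choice of cut-off moves the verified share, but not the contrast.** A reader might note that different cotinine criteria verify very different shares of children by chance, and set that against the 20-point target. The comparison fails: one criterion applied alike to both arms creates no expected difference between them when nothing has changed. Only arm-dependent application does.

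**The objective check is not lost.** The laboratory is masked, so knowledge of the arm cannot shift the assay there. Household nicotine is a further objective measure, though secondary and taken only at 0 and 12 months. Masked classification also does nothing about unblinded parental report, which may be the larger bias. All of this stands.

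**Conclusion.** The concern holds in a limited form. The article declares the whole team unblindable, describes no masked step beyond the cotinine laboratory, and gives no rule for a reduction or for verification, while counsellors see intervention-arm cotinine as it accrues. The primary classification is therefore open to arm-aware judgement. The document does not show that such judgement is made or by whom.

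It also gives neither a discordance rate nor a misclassification rate, so the bias has no derivable size. Under the assumptions of step 5 it would be 5 to 10 points, a quarter to a half of the 20-point design difference. This should be corrected because the remedy is cheap and protects the objective check on the primary outcome.

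**What to change.** 1. In the Randomisation section, limit the statement on blinding to families and to counselling and visit staff.
2. Add that primary-outcome status at each visit is derived from coded questionnaire and cotinine data without group, by one rule that the sponsor fixes before any group-labelled outcome data are examined.
3. Set the handling of discordant report and cotinine in advance, and resolve any case that the rule cannot decide with group still masked.

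The numerical cut-offs are the sponsor's choice; nothing in the article supports a particular value. They should fit an endpoint defined as exposure at home: the article recognises exposure elsewhere (the recruitment questionnaire, sessions 4 and 5), so a strict cotinine criterion could fail a family whose home is smoke-free. They should also be compatible with the 10% versus 30% assumption, since a stricter definition may lower both rates.

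The data centre that built the study database could supply the export. It belongs to the same institution as the trial and is not shown to be independent; what matters is that the group label is withheld.

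Cost: protocol wording and one masked data export. No extra staff, samples or visits are needed, and masking itself leaves the sample size unchanged.

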### Intervention program towards eliminating or reducing of PS exposure in children

In MI, the parents’ choice, personal responsibility for change, and enhancement of self-efficacy are emphasized [13]. The communication method (using open-ended questions, providing affirmation, listening reflectively and providing summaries) elicits the parents own inherent arguments for change (change talk), and increases their awareness of the discrepancy between their current behaviour and what would happen if they decide to eliminate or reduce PS exposure in their children. Counselling is focused on building motivation within parents, empathy and giving confidence to parents. Possible ambivalence with the decision to eliminate or reduce PS exposure in their children (and to stop active smoking) is discussed. Goal setting is used to help parents identify steps that they want to take to prevent PS exposure in their homes. Possible barriers experienced by the parent(s) are also discussed. As an awareness raiser, parents receive feedback from the children’s urine cotinine concentrations. The intervention program is based on the principles of the reasoned action model for the prediction and change of behaviour [30]. This model suggests that behaviour is best predicted by a person’s intention to perform certain behaviour. The intention to perform behaviour is predicted by a combination of considerations which take on different weights. These considerations are formed by a person’s: 1) beliefs towards the behaviour which determines their attitude towards the behaviour, 2) normative beliefs concerning the behaviour which produce a perceived norm concerning the behaviour, in other words, the perceived social pressure to (not) engage in a certain behaviour, and 3) control beliefs which are the person’s perceived personal and environmental factors that can facilitate or inhibit performance of the behaviour. Moreover, background factors such as past behaviour, education, and abilities also influence a person’s beliefs and resulting behaviour. These behavioural determinants are measured and considered during the sessions of the PREPASE intervention program. The intervention is given by two trained RAs and consists of 6 counselling session at home during 6 months, each lasting about 60 minutes (see Figure 1). Each family is coupled with one of the RAs. The RAs are prepared by receiving a one day training “Growing up Smoke Free (Training rookvrij opgroeien)” given by an expert from STIVORO (Dutch expert centre on tobacco control). The training includes general information regarding smoke addiction, the health effects and measures to prevent PS exposure in children, and basic training on motivational interviewing. Further coaching is given on a regular basis.

In the beginning, parents are told that our primary focus is on preventing PS exposure in children, and that quitting active smoking is not required. The intervention is tailored to whether parents are interested in reducing and/or eliminating PS exposure in their children, or if they are interested in quitting active smoking as well. If both parents of a child smoke, they are counselled together to enable a long-lasting intervention effect. If only one parent smokes, the other parent is still requested to be present during the session. The non-smoker parent may motivate the smoking parent or and reinforce his or her goals to prevent or eliminate PS exposure in their child. If parents permit, the counselling sessions are recorded on audio. The purpose of the recordings is to randomly examine the treatment fidelity. Although the intervention is tailored, a counselling protocol is developed to serve as a guideline for the counselling sessions. The following subjects are discussed:

### Session 1 - awareness of passive smoking in children

1. After an introduction by the RA details of parental smoking behaviour are assessed: number of cigarette smoked per day, possible quitting attempts in the past and the successes in these attempts, smoking behaviour inside the house and in the presence of their children. Afterwards, the parents are informed about PS exposure in children: the hazardous chemicals found in tobacco smoke, and the forms of PS exposure (second-hand smoke and third-hand smoke [31]).

2. Knowledge about the health effects of PS exposure in children is assessed and if parents want more information, this is provided.

3. Motivation and self-efficacy to prevent PS exposure in children are assessed with the importance and confidence ruler developed by Rollnick [32].

4. Parental readiness to prevent PS exposure in children is assessed. In case parents are ready to start preventing PS exposure in their children, the following subjects are discussed: measures to prevent PS exposure in children, parents’ personal goals, and, possible barriers and solutions. They are encouraged to make a ‘quit plan’ (see Table 1), that includes a quit date and their specific measures and goals. In case parents are not ready to change their behaviour, ambivalence is assessed and parents are encouraged to think about the cons and pros of preventing PS exposure in children for the following session.

5. The RA gives a summary of the session.

**Table 1 T1:** An overview of a ‘quit plan’

**Quit plan**	
***My goals are:***	•………………………………………………………‥
	• ………………………………………………………‥
***My most important reason(s) for preventing passive smoke exposure in my child is (are):***	1) ………………………………………………………
	2) ………………………………………………………
***To accomplish my goal(s), I will take the following measures:***	
Specific action:	Date:
1) ……………………	……………………………………………………………
2) ……………………	……………………………………………………………
***These are the following difficulties I may encounter and how I plan to solve them:***	
Difficulties:	Solution:
1) ……………………	……………………………………………………………
2) ……………………	……………………………………………………………
***Other person(s) that could help me achieve my goals:***	
Person(s):	How?:
1) ……………………	1) …………………………………………………………
2) ……………………	2) …………………………………………………………
***I will use the following results to ensure me that I am achieving my goals:***	• ………………………………………………………‥
	• ………………………………………………………‥

A copy of the ‘quit plan’ is included in the information booklet.

### Session 2 - preparation, planning quit-date and plan

1. The RA gives a short summary of session 1.

2. For parents who did not make a plan to quit PS exposure in their child: motivation, self-efficacy and readiness to prevent PS exposure in children are reassessed as described in session 1.3 and 1.4. Possible ambivalence, barriers and solutions are discussed. In case parents are ready, they are motivated to make a ‘quit plan’. Emphasis is put on the positive influence which the parents can have on the health of their children.

3. For parents who made a ‘quit plan’ during session 1 the ‘quit plan’ is evaluated. Self-efficacy is assessed. Difficulties parents may have encountered are also discussed. Parents are encouraged to reward themselves for their efforts. Parents may reformulate their specific goals.

4. Feedback about urine cotinine is given.

5. The RA gives a summary of the session.

### Session 3 - evaluation of the ‘quit plan’

1. The RA gives a short summary of what has been discussed previously (including possible ambivalence, barriers and solutions) and (if applicable) the specific goals parents have made to prevent PS exposure in their children.

2. The ‘quit plan’ is evaluated as described under session 2.3. Furthermore, parents have the opportunity to reformulate their specific goals or add new goals to their ‘quit plan’.

3. For parents who did not make a plan to eliminate or reduce PS exposure in their child: motivation, self-efficacy and readiness to prevent PS exposure in children are reassessed as described in session 1.3 and 1.4.

4. The RA gives a summary of the session.

### Session 4 & 5 - evaluation and focus on difficult situations

1. The RA gives a short summary of what has been discussed previously (session 3.1).

2. The ‘quit plan’ is evaluated as described under session 2.3.

3. Possible difficulties and new barriers are discussed. Parental behaviour towards difficult situations (social influences) such as visiting friends who are accustomed to smoking in the house, are further discussed. Moreover, measures to prevent PS exposure of their children elsewhere, for example when visiting grandparents, are discussed. Parents are motivated to maintain their accomplishments in eliminating or reducing PS exposure in their children. Enhancement of self-efficacy is emphasized. Parents may reformulate their specific goals.

4. Feedback about urine cotinine is given during session 4.

5. The RA gives a summary of the session.

### Session 6 - making long-term goals

1. The RA gives a short summary of what has been discussed previously

2. The ‘quit plan’ is evaluated as described under session 2.3.

3. Possible difficulties and (new) barriers are discussed as described under session 4/5.3.

4. Specific goals for the future (in order to reach a long-lasting intervention effect) are formulated.

5. Feedback about urine cotinine is given.

6. The RA gives a summary of the session and acknowledges the parents for their participation and compliments them for their efforts to prevent PS exposure in their children.

The RAs receive an extensive protocol with examples of different scenarios and how to deal with possible resistance during the sessions. Furthermore, to assist the RA during the visits, a summary of each session is given in the form of a schematic presentation; an example of session 1 is given in Figure 2.

**Figure 2 F2:**
[figure not shown]
**Schematic presentation of session 1.** *The assessment of current smoking behaviour is done during every session.

Prior to the RCT, the first two sessions of the intervention program were tested and evaluated in 11 parents who reported smoking at home in the presence of their children. Our objective was to test the feasibility of the intervention program and to gain more knowledge on the attitudes and beliefs of parents towards PS exposure in children and the barriers parents may encounter when eliminating or reducing PS exposure in their children. All parents completed the counselling sessions. Before the intervention, 6 parents (54.5%) fully agreed that eliminating PS exposure in their children is of great importance, 2 (33.3%) reported that it would be easy to accomplish. After two counselling sessions, 10 parents (90.9%) were planning to eliminate PS exposure in their children. The pilot study demonstrated good feasibility of the new intervention program. All parents were happy with the intervention style, duration, and found it relevant for parents who are smoking in the presence of their children.

